#### Economic evaluation

##### Design

The economic evaluation will compare costs and health outcomes of men in the Programme and the comparator group of men in standard care. The primary analysis will be from a health service perspective, with a secondary analysis from the patient perspective. A cost-consequence analysis will be conducted using the full range of outcome measures.

##### Data collection

Costs of the workshop and the Patient Online System will be sourced from providers. The IT costs will be annuitized over a plausible useful lifespan assuming optimal utilisation to provide a realistic cost per patient. The nurse time for monitoring and follow up using the surveillance system will be sourced from observation of a small sample of the staff performing the activity in situ. This resource use will be priced using unit costs based on national tariffs [23] or from site finance managers.

Self-reported service use data is collected in the four and 8 month questionnaires. This captures health, social and voluntary service use, including contacts with the General Practitioner, Practice Nurse, District Nurse, social worker, physiotherapist, dietician, psychologist, complementary therapies, outpatient appointments, and hospital stays. Data on routine clinic appointments and telephone contact with the urology team will be sought from site staff. Service use will be costed using national tariffs [23]. All participants will also be asked to report out-of-pocket expenses on travel to any appointments and on prostate cancer related care products and medications, and any time spent by informal carers in supporting the patient. The primary outcome measure for the economic evaluation is the EQ-5D-5 L [24] collected at all three data collection points.

##### Analysis

The average cost per patient will be calculated for both Programme and comparator groups. For the Programme group, this will comprise the workshop, the Patient Online System and associated nurse time, and the costs of all health and social care. The costs for the comparator group will comprise the cost of standard care and all other health and social care. The individual EQ-5D-5 L survey results will be used to estimate patient utility at each time point. These will be integrated over the 8 month follow up using the area under the curve method to calculate accrued quality-adjusted life years (QALYs) for each participant. Average QALY differences between groups will be estimated using ordinary least squares regression, controlling for differences in baseline utility. White adjusted standard errors will be used to account for unobserved heterogeneity.

The total cost per patient and total QALYs per patient will be compared between the Programme and comparator groups using the incremental cost effectiveness ratio (ICER). Uncertainty will be handled non-parametrically using bootstrap resampling with replacement [25]. Deterministic sensitivity analysis will be conducted around main drivers of cost, and to allow for specific uncertainties around estimated unit costs. Exploratory multivariate regression analysis will be employed to assess the relationship between health and cost outcomes and other sociodemographic data. The cost consequences analysis will compare the two service delivery models across the full range of outcomes.

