##### Recruitment

Men were recruited to the comparator group between September 2014 and June 2015, and to the Programme group between April 2015 and February 2016, with data collection completed in December 2016.

Men attending a clinic appointment who met the eligibility criteria for the evaluation were initially approached by clinical staff or a research nurse, to introduce the evaluation and to ask for consent for their contact details to be passed to the research team. Men who consented to contact were sent, by post, an introductory letter, a patient information sheet, consent form, baseline questionnaire and a freepost envelope for return of the completed documents.

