##### Data analysis

Data analysis will follow a pre-specified data analysis plan. Analyses will be conducted on an ‘intention to treat’ basis. We will first describe the baseline characteristics of participants at time T0 within each group and will compare clinical and demographic characteristics and outcome measure scores of the two groups. The same comparisons will be made with baseline data between those continuing to four and 8 month follow-up and those lost to attrition.

A regression analysis will be conducted for each of the outcome measures at the 4 month and 8 month time points separately, controlling for study site, the outcome in question if available at T0, and baseline co-variates including age, type of treatment, educational attainment, time since diagnosis, domestic status, co-morbidity, employment status, and ethnic status. If other factors differ between groups at baseline, additional controlled analyses will be carried out.

We will also estimate a mixed model including outcome at four and 8 months simultaneously, including an interaction to give separate estimates of the Programme versus standard care comparison at each follow-up point.

Finally, we will investigate whether there are any distinct subgroups for whom the intervention is effective. Guided by existing literature to indicate likely subgroup effects, separate regression analyses will be conducted for older versus younger men, men with and without co-morbidities, and men with higher and lower levels of deprivation. We will address subgroup analyses within the context of regression modelling (either linear or logistic). Interaction terms between each specified dichotomous factor (indicating subgroups) and the Programme versus standard care factor will be examined. Where interaction terms achieve statistical significance (at the 5% level), we will examine separate Programme versus comparator group estimates for each subgroup. All subgroups analyses will be considered exploratory in nature.

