## Discussion

The TrueNTH Supported Self-Management and Follow-up care Programme implements an integrated supported self-management and remote monitoring model of follow-up care within secondary care. The Programme aims to address contemporary problems with clinic capacity, but also to offer men a more tailored follow-up care experience that addresses their individual needs. While other alternatives to the clinic based model of post treatment care continue to be tested (for example, [30–32]), this Programme offers an alternative which maintains specialist oversight and input.

The Programme was funded as a service improvement initiative with accompanying evaluation. The evaluation takes a pragmatic approach [20], seeking to answer questions about effectiveness of the model within an everyday clinical setting, and also to provide information on the practicalities of implementing and sustaining such a model. Such information should provide relevant and useable conclusions for local decision makers considering implementation of a similar model in their setting [20].

There are a number of limitations to the study design. First, the use of a non-randomised comparator group represents a reduction in the ability of the study to attribute outcomes to the Programme, though the inclusion of a baseline measurement helps to address this issue, allowing for statistical adjustment of known confounders [33]. Second, men will be followed up for a period of 8 months, meaning that the study will only be able to comment on outcomes over this time period and not over a longer term [21].

Within the context of the rising number of cancer survivors, alternatives to resource intensive, medically focussed models of follow-up care are required, and supported self-management has been suggested as beneficial for cancer survivors with stable disease [34]. This evaluation of a supported self-management programme for men with prostate cancer will provide useful information for management of this particular group, but will also add to the literature on alternatives to clinic based follow-up care which will be of relevance to other groups of cancer survivors across the globe.

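### The base-case ICER is not tied to the covariate adjustment that the effectiveness analysis relies on: no covariate is named for cost, and only baseline utility for QALYs

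*Protocol article*

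**What the plan says.** The Analysis section of the economic evaluation proceeds in this order.

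- Cost: "The average cost per patient will be calculated for both Programme and comparator groups". The components of cost are listed for each group. No covariate is mentioned.
- QALYs: "Average QALY differences between groups will be estimated using ordinary least squares regression, controlling for differences in baseline utility".
- Standard errors for that regression: "White adjusted standard errors will be used to account for unobserved heterogeneity".
- ICER: "The total cost per patient and total QALYs per patient will be compared between the Programme and comparator groups", with uncertainty from a non-parametric bootstrap. The text does not say whether the adjusted QALY difference, or any adjusted cost difference, enters the ratio.
- Other factors: a multivariate regression of health and cost outcomes on sociodemographic data is planned, labelled exploratory, and not linked to the ICER.

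The Data analysis section for effectiveness treats the same men differently. Each outcome measure is regressed "controlling for study site, the outcome in question if available at T0, and baseline co-variates", and eight covariates are named: age, treatment type, education, time since diagnosis, domestic status, co-morbidity, employment and ethnicity. Further adjusted analyses follow if other factors differ at baseline.

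The Discussion accepts that "the use of a non-randomised comparator group represents a reduction in the ability of the study to attribute outcomes to the Programme" and offers baseline measurement, with adjustment for known confounders, as the partial remedy.

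**The concern.** The cohorts differ by design. The Recruitment section states: "Men were recruited to the comparator group between September 2014 and June 2015, and to the Programme group between April 2015 and February 2016". Nothing in the design balances site, treatment type or time since diagnosis between them, so the Discussion leans on covariate adjustment. The economic section does not carry that safeguard through to its main result.

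The document itself gives reasons why cost could be sensitive to this:

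- Standard care varies by hospital, as either clinic or telephone follow-up (Comparator group), and some unit costs may come from site finance managers (Data collection, economic evaluation). Site is therefore plausibly related to cost.
- The fourth site joined after five months of recruitment (Setting), so site mix may differ between cohorts.
- Men enter the Programme after a suitability assessment covering PSA criteria and functional and emotional fitness (The Programme). The evaluation's own eligibility criteria state no such screen.
- Service use is collected by questionnaire only at T1 and T2. Cost therefore has no T0 value from that source to absorb pre-existing differences, and other covariates matter more for it than for any outcome measured at T0.

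At stake is a report in which the clinical effect and the ICER come from differently adjusted comparisons of the same men.

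**Working it through.** **The plan's own figures.** The economic section gives no number to reproduce. The one computable figure in the article, the sample size, is not in dispute and serves only to size the check. With two-sided alpha 0.05 (assumed, as the article does not state it), 90% power and effect size 0.3, n = 2(1.960 + 1.282)²/0.3² = 233.5, so 234 per group against the stated 235. Power at 235 is 90.2%, and 235/0.80 = 294, consistent with around 300.

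**Adjustment as stated**

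| Quantity | Covariates named | Status |
|---|---|---|
| Each outcome measure at T1 and T2 | Site, T0 value where available, eight baseline covariates | Main analysis |
| QALY difference | Baseline utility | Main analysis |
| Cost difference | None | Main analysis |
| Health and cost on other factors | Sociodemographic data | Exploratory |
| ICER | Totals per patient; adjustment not stated | Main result |

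**Can site mix differ?** Assume equal monthly accrual at every site, and count the five months from September 2014. Comparator recruitment ran 10 months, giving 3 × 10 + 5 = 35 site-months, of which the fourth site supplies 5/35 = 14%. Programme recruitment ran 11 months, giving 4 × 11 = 44 site-months, of which it supplies 11/44 = 25%. The gap is about 11 percentage points. This shows that imbalance is plausible, not that it occurred.

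**Do White errors or the bootstrap help?** Take 235 men per group, a true Programme effect of zero, and a baseline value in the model explaining 0.25 of the variance. Omit one further factor that differs between cohorts by s SD and affects the outcome by b SD per SD. Both s and b are assumptions. The group estimate is biased by s × b. With residual variance 0.75, its standard error is √(0.75 × 2/235) = 0.080.

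- s = b = 0.3: bias 0.09 SD. 0.09/0.080 = 1.13 standard errors, so the formula gives a false-positive rate of about 20%. Simulation with 2,000 runs gave 17.8% under both classical and White errors; a check with 20,000 runs gave 19.9% under both.
- s = b = 0.1: bias 0.01 SD. The rate is about 5 to 6% with either error.
- s = b = 0.5: bias 0.25 SD. The rate is about 86 to 88% with either error.
- With the factor added to the model, bias was 0.00 and the rate 4.8 to 6.0% in all settings.

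In the 2,000-run simulations the classical and White rates never differed by more than 0.1 percentage point. White errors change the estimated variance and leave the coefficient alone. A bootstrap of the same unadjusted quantity is likewise centred on the biased value.

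**How a cost bias reaches the ICER.** Holding the QALY difference fixed, shift in ICER = cost bias / QALY difference. None of the inputs below comes from the document.

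- Cost bias = difference in mix × cost difference between categories = 0.10 × £500 = £50 per man. With £200 to £1,000 in place of £500, it is £20 to £100.
- £50/0.01 = £5,000 per QALY. With QALY differences of 0.02 and 0.005, it is £2,500 and £10,000.
- At a QALY difference of 0.01, the £20 to £100 range gives £2,000 to £10,000 per QALY.

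**The case against.** The case on the other side has four parts.

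1. **The economic result is not effectively unadjusted.** A reader might infer that it is, but the QALY difference is adjusted for baseline utility, usually a key covariate for a QALY difference. The natural reading is that this estimate feeds the ICER, even though the ICER sentence does not say so. For cost, the article says averages will be calculated; it never says that covariates are excluded. This objection stands against the stronger reading.

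2. **Adjusted results for related quantities are already planned.** Table 1 lists EQ-5D-5L and health service use among the outcome measures, so the effectiveness regressions cover both. This also stands, but those regressions are not linked to the ICER.

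3. **The White sentence is probably loose wording.** A reader might infer that the authors credit White errors with removing unobserved differences between cohorts. The sentence concerns standard errors, and the Discussion gives the task of handling confounding to baseline adjustment. If heteroskedasticity is meant, the method is suitable and only the phrase is wrong. This stands.

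4. **This is a condensed article with an analysis plan not shown.** A fuller covariate list could sit there. This lowers confidence but does not dispose of the point. The article does name covariates for the QALY model and gives one. It also assigns regression on other factors to an exploratory role. A plan that adjusted the main economic comparison fully would depart from that description.

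**Conclusion.** The point holds as a mismatch within the article. The effectiveness analysis and the Discussion depend on adjusting for site and known confounders, while the main economic result is not tied to that adjustment. Taken as written, imbalance in site, treatment type or time since diagnosis would pass into incremental cost and the ICER, and to a lesser extent into QALYs beyond what baseline utility absorbs.

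The size and direction of any bias cannot be determined from the document. The pound figures and the simulated error rates rest on assumed inputs and show the mechanism only. In particular, the suitability screen does not establish that unadjusted costs would favour the Programme. Covariate adjustment would also leave unmeasured differences between cohorts in place, a limitation that the Discussion already accepts.

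**What to change.** - State that the base-case ICER uses cost and QALY differences both adjusted for study site and the covariates of the effectiveness model, plus T0 utility for QALYs.
- First confirm that co-morbidity is collected. It is named as a covariate, but neither the Data collection section nor Table 1 lists it among the data gathered. The other seven can be drawn from the listed medical-record and demographic items.
- Refit the adjusted regressions within each bootstrap sample, so that the uncertainty belongs to the adjusted ICER.
- Report unadjusted mean costs and QALYs as descriptive.
- Reword the White sentence to say that these errors allow for heteroskedasticity.

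The form of the cost model can be left to the analysts. Baseline cost cannot be added as a covariate from the questionnaires, because service use is not asked at T0. The change costs some wording and a small amount of extra analysis, with no new data if co-morbidity is already held.

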#### Assessing implementation

##### Design

The aim of this component of the evaluation is to assess the process of implementation of the Programme and to identify any barriers and facilitators to implementation. Data are being collected though semi-structured interviews with staff involved in service delivery or management, and with a subsample of men taking part in the questionnaire study. Normalisation Process Theory (NPT) [26] is being used to sensitise the interviews to factors which may help or hinder the embedding of the Programme at the sites.

##### Data collection

Semi-structured interviews are completed with a sample of up to 10 staff from each of the four study sites. Both clinical and managerial staff involved with the Programme were identified through discussion with the lead clinician and lead nurse at each site. These interviews are conducted by telephone and focus on experiences of implementing the Programme.

Similarly, interviews are being conducted with a maximum of 12 men from each of the four study sites, to include men who have experienced standard care (maximum of four men per site) and men enrolled in the Programme (maximum of eight men per site). The interview guides for both patients and staff are provided in Additional file 1. Men were purposively selected from those who indicated on their baseline questionnaire that they were happy to be contacted regarding an interview. The sample was selected to take account of age, type of cancer treatment, time since diagnosis and computer usage. The interviews focus on men’s experience of follow-up care and the post treatment period, and take place by telephone or face-to-face according to preference.

##### Analysis

Each audio-recording is transcribed verbatim and is checked against the recording. The analysis is taking a team approach. The initial coding frame was developed through a process of independent coding and subsequent discussion of a number of transcripts by at least two of the study team. The development of codes took both a deductive and inductive approach, having an initial focus on the research question, NPT constructs and the underlying theory of change, but also being open to codes that emerge from the data. The reliability of the individual coders was established over a number of transcripts and then the coding frame will be applied to remaining transcripts. Analysis will involve the constant comparison of data and close attention to deviant cases. Regular evaluation team meetings will be held to reach consensus on themes and findings.

##### Ethics and reporting

The study received ethical approval from the National Research Ethics Service, East of England – Cambridge South (reference number 11/EE/1021), research governance approval from the individual NHS Trusts involved with the study, and has been adopted by the National Institute of Health Research Clinical Research Network (ID 17238). Study reporting will follow appropriate guidelines [27–29].

## Discussion

The TrueNTH Supported Self-Management and Follow-up care Programme implements an integrated supported self-management and remote monitoring model of follow-up care within secondary care. The Programme aims to address contemporary problems with clinic capacity, but also to offer men a more tailored follow-up care experience that addresses their individual needs. While other alternatives to the clinic based model of post treatment care continue to be tested (for example, [30–32]), this Programme offers an alternative which maintains specialist oversight and input.

The Programme was funded as a service improvement initiative with accompanying evaluation. The evaluation takes a pragmatic approach [20], seeking to answer questions about effectiveness of the model within an everyday clinical setting, and also to provide information on the practicalities of implementing and sustaining such a model. Such information should provide relevant and useable conclusions for local decision makers considering implementation of a similar model in their setting [20].

There are a number of limitations to the study design. First, the use of a non-randomised comparator group represents a reduction in the ability of the study to attribute outcomes to the Programme, though the inclusion of a baseline measurement helps to address this issue, allowing for statistical adjustment of known confounders [33]. Second, men will be followed up for a period of 8 months, meaning that the study will only be able to comment on outcomes over this time period and not over a longer term [21].

Within the context of the rising number of cancer survivors, alternatives to resource intensive, medically focussed models of follow-up care are required, and supported self-management has been suggested as beneficial for cancer survivors with stable disease [34]. This evaluation of a supported self-management programme for men with prostate cancer will provide useful information for management of this particular group, but will also add to the literature on alternatives to clinic based follow-up care which will be of relevance to other groups of cancer survivors across the globe.

## Abbreviations

CNS: Clinical Nurse Specialist
HNA: Holistic Needs Assessment
ICER: Incremental cost effectiveness ratio
IT: Information technology
NCSI: National Cancer Survivorship Initiative
NHS: National Health Service
PADT: Primary androgen deprivation therapy
PSA: Prostate specific antigen
QALY: Quality-adjusted life year
SSM: Supported self-management
T0: Baseline assessment point
T1: 4 month assessment point
T2: 8 month assessment point
